#### Interim analyses

An interim-analysis is performed on the primary endpoint when 50% of patients have been randomized and have completed the interventions. The interim-analysis is performed by an independent statistician, blinded for the treatment allocation. The statistician will report to the independent data monitoring committee. The data monitoring committee will have unblinded access to all data and will discuss the results of the interim-analysis with the steering committee in a joint meeting. The steering committee decides on the continuation of the trial and will report to the central ethics committee.

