### Study setting

The study will include four sites in Hunan, China. They are First Affiliated Hospital of Hunan University of Chinese Medicine, Changsha Chinese Medicine Hospital, Yueyang Chinese Medicine Hospital, and Chenzhou Chinese Medicine Hospital. Other sites may be added for participation in the study. Sites that do not enroll any subjects within 3 months of site initiation will be closed. Each site must follow this study protocol; otherwise, it will be closed. The Steering Committee will audit and review the intervention performed in each site, to ensure that they are following this protocol.

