### Statistical methods

#### Dataset analysis

For the primary endpoint of percentage change in LDL-C from baseline, the efficacy of acupuncture and moxibustion will be evaluated at week 12 by comparing the treatment effect to that of the active control group. A type I error of 0.05 will be allocated to the test.

There are three main analysis sets:Full analysis set (FAS): includes all randomized subjects who have received at least 1 investigational treatmentCompleter Analysis Set (CAS), includes subjects in the FAS who completed their scheduled intervention and have a nonmissing LDL-C value at week 12Effect Durability Analysis Set (EDAS), includes subjects in the FAS who completed their scheduled intervention and have non-missing LDL-C values at week 6 and week 12

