### Data monitoring

A Data Monitoring Committee (DMC) has been established. The DMC is independent of the study organizers. During the period of recruitment to the study, interim analyses will be supplied, in strict confidence, to the DMC, together with any other analyses that the committee may request. This may include analyses of data from other comparable trials. In the light of these interim analyses, the DMC will advise the trial steering committee when:The active intervention has been proved, beyond reasonable doubt, to be different from the control (standard management) for all or some types of participants, andThe evidence on the outcomes is sufficient to guide a decision from the health care providers

The Trial Steering Committee can then decide whether or not to modify intake to the trial. Unless this happens, however, the Steering Committee will remain ignorant of the interim results.

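### The protocol contradicts itself on whether the steering committee sees the half-way comparative results, and its trigger for advice does not match the noninferiority question

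*Protocol article*

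**What the plan says.** - **Interim analyses.** One look is scheduled: "An interim-analysis is performed on the primary endpoint when 50% of patients have been randomized and have completed the interventions". An independent statistician, blinded to allocation, reports to the data monitoring committee (DMC). The DMC has unblinded access to all data and "will discuss the results of the interim-analysis with the steering committee in a joint meeting". After that, "The steering committee decides on the continuation of the trial and will report to the central ethics committee". No condition is attached to the meeting.
- **Data monitoring.** Interim analyses, and any others the DMC asks for, go to the DMC confidentially during recruitment. The DMC advises the steering committee when two joined conditions are met. The first is that the active intervention "has been proved, beyond reasonable doubt, to be different from the control (standard management"). The second is that the evidence is good enough to inform providers' decisions. The steering committee may then change intake. The section ends: "Unless this happens, however, the Steering Committee will remain ignorant of the interim results".
- **Study setting.** "The Steering Committee will audit and review the intervention performed in each site".
- **Dataset analysis.** For the week-12 primary comparison, "A type I error of 0.05 will be allocated to the test".
- **Trial design and Blinding.** The trial is an open-label noninferiority trial in which neither participants nor care providers are blinded.

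**The concern.** Two current sections give opposite instructions on access to unblinded comparative results for the primary endpoint. The body in question is not remote from the trial: it audits how the intervention is delivered at each site, can change intake, and decides whether the trial goes on. Treatment is open, so a steering committee that knows which arm is ahead at the half-way point could alter recruitment effort, site oversight or the decision to continue, even unintentionally. Disclosure cannot be undone once the meeting has taken place.

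A lesser concern is the trigger for advice. The trial asks whether acupuncture and moxibustion is noninferior to simvastatin on LDL-C. The trigger asks whether the arms differ, in no stated direction, so the document does not make clear what an interim finding may be used to claim.

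**Working it through.** **1. The two sections side by side**

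| Outcome of the half-way look | Interim analyses section | Data monitoring section |
|---|---|---|
| Trigger not met | DMC discusses the results with the steering committee, which decides on continuation | Steering committee is not told the results |
| Trigger met | The same | DMC advises; steering committee may change intake and may learn the results |

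The rows agree only when the trigger is met. When it is not met, following one section breaches the other. An unseen DMC charter could not cure this, because it would have to depart from one of them.

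Appendix 2 (Lipid Measurements) also keeps investigators, subjects and the study team blinded to post-randomization lipid values until the database is unblinded. If steering committee members count as study team, which the document does not say, the joint meeting conflicts with that rule too.

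**2. The plan's own sample size**

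Inputs from the Sample size section: difference 0.343, SD 0.7, power 0.80, and a stated level of 0.95, read as alpha 0.05 two-sided.

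n per group = 2 × (1.960 + 0.842)² × 0.7² / 0.343² = 2 × 7.85 × 0.49 / 0.1176 ≈ 65.4, which rounds up to 66.

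The plan states about 65, so it reproduces. The formula is for a fixed sample and contains no allowance for an interim test.

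**3. What the interim look could do to the error rate**

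The document gives no interim threshold, so the thresholds here are assumptions. With one look at information fraction t = 0.5, the interim and final statistics have correlation √0.5 = 0.707. If the final test is at two-sided 0.05, the overall chance of declaring a difference when there is none is 1 − P(|Z₁| < c₁, |Z₂| < 1.96).

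| Assumed interim threshold (two-sided) | c₁ | Overall error |
|---|---|---|
| P<0.001 | 3.29 | 0.0502 |
| P<0.05 | 1.96 | 0.083 (0.086 at t = 0.4; 0.080 at t = 0.6) |

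These rows apply to a claim of difference. For noninferiority the argument needs no boundary. If the interim look can never end in a noninferiority claim, the only route to a false one is the final test, so the error rate for that claim cannot exceed the level of the final test.

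**The case against.** **Measurement is protected.** LDL-C is measured by a central laboratory, and outcome assessors and data analysts are blinded. This stands: the risk is to recruitment, delivery and the continuation decision, not to the assay. The document does not show that auditing compliance would in fact change the result. It leaves the route open.

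**A reader might infer that the interim is tested at 0.05 and that the type I error is 8.3%.** The document does not say so. The 0.05 is assigned to the week-12 test, and the trigger's standard of proof, together with its second condition, suggests something stricter. A numerical boundary may sit in an analysis plan or DMC charter that is not shown, so its absence from a journal article is not a finding. The 8.3% is an upper illustration for a single look.

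**A reader might infer that the trial stops on a superiority criterion.** That is not supported either. The trigger leads to advice and a possible change of intake, and it has no direction, so it also covers inferiority and harm. The power to decide on continuation comes from the Interim analyses section, which gives no criterion.

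**A difference trigger hardly affects the noninferiority error.** This is largely right. The document states no margin; take 0.343 as one by assumption. With 130/2 = 65 patients, about 32 per arm, the SE is 0.7 × √(2/32.5) ≈ 0.174 and the margin is 0.343/0.174 ≈ 1.97 SE. If the truth lies at the margin, the chance of showing superiority at the look is P(Z > 1.96 + 1.97) ≈ 0.00004. The mismatch is therefore about what an interim finding may be used for, not a demonstrated inflation.

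**Conclusion.** The contradiction over steering committee access holds on the text alone and needs no assumption. It should be resolved before the half-way look. Its consequence is an avoidable route to operational bias in an open-label trial, and the document gives nothing from which to put a size on that bias.

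The trigger mismatch is secondary. The document does not support saying that type I error is uncontrolled. For a claim of difference, with one look at half information and the final test at 0.05, the overall error would lie between about 0.0502 and 0.083 for assumed interim thresholds from P<0.001 to P<0.05. The upper end applies only if the interim were itself tested at two-sided 0.05. If no early noninferiority claim is allowed, the final test needs no adjustment for that claim.

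**What to change.** - **Interim analyses:** keep the DMC's unblinded access, but delete the wording on the joint meeting. State that the DMC reviews the closed results and sends the steering committee only a recommendation: continue, modify or stop. The steering committee can still decide on continuation, acting on that recommendation. This agrees with the Data monitoring section.
- **Data monitoring:** state that the interim look supports no early claim of noninferiority, and that the final test stays at 0.05.
- **Optional:** name a strict interim threshold. Two-sided P<0.001 is one choice. Boundaries that hold 0.05 at t = 0.5, as nominal two-sided P at interim / final, are O'Brien-Fleming (0.0052 / 0.0480), Lan-DeMets of O'Brien-Fleming type (0.0031 / 0.0490) and Pocock (0.0294 / 0.0294). With any of these three, the final level would be the one listed in place of 0.05.

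The cost is a few sentences in two sections. The first two changes require no extra patients or staff. They need to be made before the half-way look, because disclosed results cannot be withdrawn.

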#### Consistency analysis

To evaluate the consistency of the treatment effect of acupuncture and moxibustion, the following analyses will be performed:Consistency of treatment effects (acupuncture and moxibustion versus simvastatin) of week 6 and week 12: the 95% CI of the difference of the treatment effect at week 6 and the treatment effect at week 12 will be provided from the repeated measure mixed-effect model. The estimations will be from the FAS and the EDASLDL change from week 6 to week 12:the treatment effect of percentage change from week 6 to week 12 will be estimated by using an ANCOVA model. The estimation of 95% CI will be based on the EDAS

Analysis of other secondary efficacy endpoints will be similar to the primary analysis of the primary endpoint. All tests will be based on a significance level of 0.05, without adjustment for multiple endpoints.

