### Outcome measurements

#### Primary outcome

The primary outcome is the percentage change from baseline to the end of the study (after the 12-week intervention and after another 4-week follow-up) in LDL-C. The calculated LDL-C concentration will be determined at screening (entry to the study), day 1 (after TLC is completed and eligibility is determined), week 6, and week 12. LDL-C will be measured by preparative ultracentrifugation by the central laboratory. The LDL-C concentration calculated at screening will be reported only for the eligibility decision. The baseline lipid measurements for the purpose of analysis will be the day-1 lipid measurement after TLC (lipid stabilization). This will be collected after a ≥9-h fast and before receiving intervention.

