#### Statistical analysis plan

The primary analysis set for the primary endpoint is the FAS. It is to use the repeated measures, linear mixed-effects model, including terms for treatment group, stratification factor, baseline LDL-C, scheduled visit and the interaction of treatment with scheduled visit. Missing values will not be imputed when the repeated measures, linear mixed-effects model is used.

We will use the chi-squared test for binary outcomes, and the *t* test for continuous outcomes. For subgroup analyses, we will use regression methods with appropriate interaction terms (respective subgroup treatment group). Multivariable analyses will be based on logistic regression for binary outcomes and linear regression for continuous outcomes. We will examine the residual to assess model assumptions and goodness-of-fit. For timed endpoints, such as mortality, we will use the Kaplan-Meier survival analysis followed by the multivariable Cox proportional hazards model for adjusting for baseline variables. We will calculate Relative Risk (RR) and RR Reductions (RRR) with corresponding 95% confidence intervals to compare dichotomous variables, and difference in means will be used for additional analysis of continuous variables. *P* values will be reported to four decimal places with *P* values < 0.05 reported as *P* < 0.05. Up-to-date versions of R (R Foundation) will be used to conduct analyses. For all tests, we will use two-sided *P* values with alpha no greater than 0.05 level of significance. We will use the Bonferroni method to appropriately adjust the overall level of significance for multiple primary outcomes, and secondary outcomes.

In investigation of the robustness of the analysis results, the primary analysis will be repeated using the CAS. In addition, parametric analysis of covariance (ANCOVA) and appropriate nonparametric methods will be used on the FAS, in which missing data will be imputed using the last-observation-carried-forward (LOCF) approach. The primary analysis will also be repeated for subgroups of interest.

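### Two sections give conflicting multiplicity rules for the five secondary efficacy outcomes (Bonferroni or unadjusted 0.05), and the P-value reporting rule hides which threshold a result met

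*Protocol article*

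**What the plan says.** All references are to the protocol article.

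- **Statistical analysis plan section:** "We will use the Bonferroni method to appropriately adjust the overall level of significance for multiple primary outcomes, and secondary outcomes". The number of tests in the family is not given. The same section sets the general level: "For all tests, we will use two-sided *P* values with alpha no greater than 0.05 level of significance".
- **Consistency analysis section:** after "Analysis of other secondary efficacy endpoints will be similar to the primary analysis of the primary endpoint", the next sentence reads "All tests will be based on a significance level of 0.05, without adjustment for multiple endpoints".
- **Reporting rule (Statistical analysis plan section):** "P* values will be reported to four decimal places with *P* values < 0.05 reported as *P* < 0.05".
- **Primary endpoint:** the Dataset analysis section places the comparison at week 12 and says "A type I error of 0.05 will be allocated to the test".
- **Claims at stake:** the Hypotheses section lists noninferiority on percentage change in LDL-C (the primary) and on the five efficacy outcomes that the Secondary outcomes section names: absolute LDL-C change, percentage change in HDL-C, TC and TG, and the LDL-C goal rate. It also lists superiority on safety and tolerability, and on adherence.

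**The concern.** One sentence requires adjustment of the secondary outcomes and another forbids it for the secondary efficacy endpoints. The article does not say which prevails. The outcomes concerned carry stated hypotheses, so the choice decides which noninferiority claims the trial may make. While both sentences stand, the threshold can be chosen after the results are known.

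The reporting rule adds to this. Four decimals would be kept only for results that are not significant at 0.05. A P of 0.04 and a P of 0.0001 would look the same in print, so a reader could not tell whether a Bonferroni level had been met.

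**Working it through.** **1. What the plan's own sample size assumes.** Inputs from the Sample size section: difference 0.343 and SD 0.7, both for absolute LDL-C change; power 0.80. The stated significance level of 0.95 is read here as alpha 0.05 (an assumption). With a two-sided test,

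n per group = 2 × [0.7 × (1.960 + 0.842) / 0.343]² ≈ 65.4, which rounds up to 66.

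This agrees with the stated figure of about 65. A one-sided 0.05 test would give 52 and does not agree. The sample size therefore rests on one unadjusted two-sided 0.05 test (equivalently one-sided 0.025).

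**2. The two thresholds.** Five secondary efficacy outcomes, counted from the Secondary outcomes section:

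- Bonferroni: 0.05 / 5 = 0.01 each, or 99% confidence intervals.
- No adjustment: 0.05 each, or 95% confidence intervals.

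A P value of 0.05 or more fails under both rules, and one below 0.01 passes under both. The rules disagree only between 0.01 and 0.05. Because the family is not defined, the lower end can move: 0.05 / 6 = 0.0083 with a sixth test, 0.05 / 7 = 0.0071 with a seventh.

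**3. Family error if nothing is adjusted, two-sided difference tests.** Under independence it is 1 − 0.95^k; under any dependence it is at most 0.05k.

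| Tests k | Bonferroni level | Error, independent | Bound |
|---|---|---|---|
| 5 | 0.0100 | 0.226 | 0.25 |
| 6 | 0.0083 | 0.265 | 0.30 |
| 7 | 0.0071 | 0.302 | 0.35 |

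**4. The same for noninferiority claims.** A false noninferiority claim read from a two-sided 95% interval has probability 0.025. For five claims:

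- independent: 1 − 0.975^5 = 0.119;
- bound: 5 × 0.025 = 0.125.

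Independence is not realistic. Absolute LDL-C change and goal attainment come from the same measurement, and total cholesterol includes LDL-C.

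**5. The primary.** The Primary outcome section defines one outcome. The Dataset analysis section fixes its comparison at week 12 with 0.05. No sentence divides that 0.05 among the primary and the secondary outcomes.

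**The case against.** **The conflict is narrow.** The no-adjustment sentence stands under a heading about consistency of effect and could be meant for those analyses alone. That reading does not hold: the sentence before it names the secondary efficacy endpoints, and it speaks of multiple endpoints. It is true, though, that the disagreement touches only P values between about 0.01 and 0.05.

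**This belongs in a separate analysis plan.** A missing detail could be left there. Here the article states two rules, and any later plan would have to contradict one of them.

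**The reporting rule may be a slip.** It asks for four decimals and then removes them below 0.05, so a smaller cut-off may have been intended. The article also plans 95% confidence intervals for dichotomous comparisons and for the consistency analyses, so some P values could be recovered. This weakens the reporting point but does not remove it; the rule as written still needs correcting.

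**Stronger readings that the article does not support.**

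- A reader might infer that success on the primary is also undetermined. The mention of multiple primary outcomes in the Bonferroni sentence invites this, as does the Primary outcome section, which names a time after 12 weeks and another 4 weeks later. But there is one primary outcome, and the Dataset analysis section gives its week 12 test 0.05.
- A reader might infer that Bonferroni over six outcomes cuts power for the primary to about 0.56 at 65 per group. That needs a pooling which the text does not state. It also uses a difference and SD for absolute LDL-C change, a secondary outcome; none are given for percentage change.
- A reader might apply the 23% to the noninferiority claims. For claims read from 95% intervals the figure is about 12%.

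**Conclusion.** The contradiction is real and confined to secondary outcomes. For the five secondary efficacy outcomes the success threshold is either 0.01 or 0.05, and the article does not say which. The cost of leaving them unadjusted is a family error of about 23% (bound 25%) for two-sided difference tests, or about 12% (bound 12.5%) for noninferiority claims. The first figure of each pair assumes independence; the bounds need no such assumption. The count of five is taken from the Secondary outcomes section, since the article does not define the family.

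The rule for printing P values would hide which threshold was met. The primary outcome is not clearly affected, and no loss of power for it can be derived from the figures given.

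**What to change.** Settle the following before outcome data are seen:

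1. Keep one multiplicity rule and delete the contrary sentence.
2. State that the primary, percentage change in LDL-C at week 12, lies outside the Bonferroni family and keeps the 0.05 of the Dataset analysis section, subject to any alpha spent at the interim look in the Interim analyses section.
3. For the five secondary efficacy outcomes, either apply the retained adjustment (Bonferroni at 0.01 each, or Holm, which is uniformly more powerful), or label them unadjusted and supportive.
4. Say how the superiority hypotheses on safety, tolerability and adherence are handled, so that they are neither left out nor demoted without comment.
5. Report exact P values to four decimals, truncating only those below 0.0001.

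This changes wording only and needs no added patients, visits or measurements. The price of adjusting is that some secondary claims become harder to make. As an illustration, take the Sample size section's figures for absolute LDL-C change and 65 per group. Power is Φ(√(65/2) × 0.343/0.7 − z), where √(65/2) × 0.343/0.7 = 2.793. At 0.05 this is Φ(2.793 − 1.960) ≈ 0.80; at 0.01 it is Φ(2.793 − 2.576) ≈ 0.59.

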#### Safety summaries and adherence analysis

Safety summaries will include the subject incidence of AEs, summaries of laboratory parameters, vital signs, and ECGs.

### Data monitoring

A Data Monitoring Committee (DMC) has been established. The DMC is independent of the study organizers. During the period of recruitment to the study, interim analyses will be supplied, in strict confidence, to the DMC, together with any other analyses that the committee may request. This may include analyses of data from other comparable trials. In the light of these interim analyses, the DMC will advise the trial steering committee when:The active intervention has been proved, beyond reasonable doubt, to be different from the control (standard management) for all or some types of participants, andThe evidence on the outcomes is sufficient to guide a decision from the health care providers

The Trial Steering Committee can then decide whether or not to modify intake to the trial. Unless this happens, however, the Steering Committee will remain ignorant of the interim results.

